### Procedure

Participation in the study includes four stages. The stages and their timeline is as shown in the flow diagram. Once the participant expresses interest and provides consent, the primary author will contact them to collect the baseline data and confirm their attendance at the in-person event. The intervention involves a half-day in-person event and identical demo sessions with a maximum of six participants in each session will be conducted. The maximum number of participants per session was determined per the recommendation of agridemo guidelines [35, 48] and feedback from the informal demo session. Participants can choose to participate in any one of the sessions based on their convenience. At the end of the intervention, participants will be asked to complete an exit survey to share their feedback about the intervention (see Additional file 5 for an example exit survey). The primary author will send an SMS survey after 7 days to monitor the participant’s progress in the adoption of safety goals (target behaviours). All participants will be invited to take part in an online interview within 20 days of the intervention to assess the perceived acceptability of the intervention among participants.

#### Materials

The participants will be provided with all materials to implement the safety strategies demonstrated and discussed in the intervention session.

### Data collection

#### Baseline assessments

The primary author will collect demographic data and the safety devices currently used by the participant during the introductory session (stage 1) using a pre-prepared questionnaire (see Additional file 1 for an example questionnaire).

#### Follow-up assessments

Immediately after completing the intervention session, participants will be requested to fill out an anonymous exit survey. An exit survey is a modified version of the feedback form provided as a part of the EU H2020 AgriDemo [35, 40, 48]. The objective of this survey is to gather participants’ immediate feedback on the acceptability of intervention components. This information may also help to gain the feedback of participants who may drop out before the post-intervention interview and is expected to support the researchers in refining the interview guide for the qualitative interview. The convenient time to receive the SMS survey and set up the interview would also be collected at the end of the session.

The SMS survey is intended to remind and track the progress made by the participants on the adoption of the safety goals at their farms. The follow-up evaluation interview will be a 1-h semi-structured online interview to explore perceived acceptability, measure receipt of treatment and enactment of skills (see Additional file 6 for an example topic guide). While the SMS survey measures the progress on the completion of safety goals (home-based tasks), the interview will further explore their experience with performing the tasks at home and if they faced any barriers to completing the activities.

### Study outcomes and measures

A summary of the objective, measures and tools to assess the outcomes are provided in the table.

#### Feasibility outcomes

Consideration of feasibility criteria was guided by the agriculture literature and feasibility study guidelines [29, 49]. Feasibility will be measured based on the criteria detailed in Table 1.

**Table 1 Tab1:** Data collection and evaluation plan

**Objective**	**Indicators and outcome measures**	**Data collection method**	**Measure of success**
**Feasibility Checklist**			
**Feasibility**	Recruitment rate: % of participants recruited/time	Recruitment report by the Teagasc.	**Recruitment:** Successfully recruit a minimum two farmers from each of the four farm types: dairy, beef, sheep and tillage
	Retention and follow-up rates: % of participants completed the stage 1, stage 2, stage 3, stage 4 (Fig. 1)	Audio recording of the in-person sessions Intervention checklist (Additional file 1)	
	Time required to recruit target sample size: 16 participants recruited/time	Recruitment report by the Teagasc	
	Adherence rates: % of participants completed the stage 1, stage 2, stage 3, stage 4	Field notes and Memos from the in-person sessions	**Retention rate:** 80% of the participants complete the in-person session & A minimum of 12 participants complete follow-up interviews
	Rate of completion of the intervention: % of intervention activities completed by the participants	Field notes and Memos from the in-person sessions	
		SMS Survey	
	Representation of farm population: % of participants recruited from four farm types/total participants	Pre-intervention interview data	
	Barriers & facilitators to set up the in-person event: Factors identified by the facilitators	Recruitment report by the Teagasc Audio recording of the in-person sessions Field notes from the in-person sessions	**Programme structure:** At least 80% of the participant rate the programme structure and content as satisfactory
	Is the structure of the programme (length of the event, structure and content of the intervention) realistic, clear and reasonable for the participants?: Average score for each of the responses in the exit survey	Exit survey	
		Post-intervention interview	
	The ability of the participants to carry out the target behaviours (safety behaviours) addressed in the study: Participants’ feedback about their experience	Safety training procedure Exit survey Post-intervention interview	
**Fidelity Checklist** (1)			
**Fidelity: **Intervention Design	1—Provide information about treatment dose in the intervention condition: Detailed information about the intervention is presented in the intervention checklist, such as: a. Length of session b. Number of sessions c. Content of each session d. Duration of contact over time	Intervention checklist	**Intervention report**: Detailed report on the development of the intervention, content of the intervention and BCTs included in it using TiDier checklist
	2 Theoretical model upon which the intervention is based is clearly articulated in the methodology paper and includes the following information: a. The active ingredients are specified and incorporated into the intervention b. Use of experts or protocol review group to determine whether the intervention protocol reflects the underlying theoretical model or clinical guidelines c. Plan to ensure that the measures reflect the hypothesised theoretical constructs/mechanisms of action	A manuscript describing the development of BeSafe Intervention	**Trial registration:** Register the study on ISRCTN registry
	3 Potential confounders that limit the ability to make conclusions at the end of the trial are identified?	Post-intervention interview	
	4 Plan to address possible setbacks in implementation (i.e. back-up systems or providers)	Risk assessment document	
**Fidelity: **Treatment providers*	1 Description of how providers will be trained (manual of training procedures)	Intervention manual	**Intervention manual:** Complete and upload the intervention manual in a public repository
**Fidelity: **Treatment delivery	1 Method to ensure that the content of the intervention is delivered as specified (content, dose, process): Number of intervention components delivered as intended/Number of intervention components expected to be delivered	Audio recording Intervention checklist Field notes	**Delivery**: A minimum of 80% of the intervention components presented in the intervention checklist are delivered.
	2 Assessment of non-specific treatment effects: Participants report on the experience of the programme vs expected outcome	Post-intervention interview	
	5 Use of Intervention manual	Project information sheet	
	6 There is a plan for the assessment of whether or not the active ingredients were delivered: Number of active ingredients delivered as intended/Number of active ingredients present in the BeSafe intervention	Audio recording Intervention checklist Field notes	
	7 There is a plan for the assessment of whether or not proscribed components were delivered. (e.g. components that are unnecessary or unhelpful)	Audio recording Intervention checklist Field notes	
	8 There is a plan for how will contamination between conditions be prevented	N/A	
	9 There is an a priori specification of treatment fidelity (e.g. providers adhere to delivering > 80% of components): Reference to ‘measure of success’ column	Data collection and evaluation plan	
**Fidelity: **Receipt of Treatment	1 There is an assessment of the degree to which participants understood the intervention: Participants’ report on their understanding of the intervention skills	Safety training procedure Exit poll Post-intervention interview	**Receipt:** A minimum of 60% of the participants complete the target behaviours at home
	2 There are specifications of strategies that will be used to improve participant comprehension of the intervention: Completion of tailored plan using the safety training procedure document an participants’ feedback	Safety training procedure Exit poll Post-intervention interview	
	3 The participants’ ability to perform the intervention skills will be assessed during the intervention period: Self-report on the confidence in completing the target behaviours and participants’ feedback	Safety training procedure Exit poll Post-intervention interview	
	4 A strategy will be used to improve subject performance of intervention skills during the intervention period: Hands-on practice session on demonstration, completion of tailored plan using the safety training procedure and participants’ feedback	Peer to peer demo Safety training procedure	
	5 Multicultural factors considered in the development and delivery of the intervention (e.g. provided in native language; protocol is consistent with the values of the target group)	N/A	
**Fidelity: **Enactment of Treatment Skills	1 Participant performance of the intervention skills will be assessed in settings in which the intervention might be applied: Participants’ self-report on the completion rate of safety goals (target behaviours)	SMS Survey Post-intervention interview	
	2 A strategy will be used to assess performance of the intervention skills in settings in which the intervention might be applied: Participants’ reported experience on completing the safety goals at home	Post-intervention interview	
**Acceptability checklist**			
**Retrospective acceptability**	1 Affective attitude (How did the participant feel about the programme): Average satisfaction score for the programme in the exit survey	Safety training procedure Exit survey Follow-up evaluation interview	A minimum of 80% of the participants rate the programme on exit survey as “Agree” or “Strongly agree” A minimum of 80% of the participants rate their confidence in completing safety goals at least 7 out of 10
	2 Burden (What did the participants say about the structure and ease to understand): Average satisfaction score for the programme structure in the exit survey and participants’ feedback		
	3 Ethicality (To what extent the strategy helped in performing the farm tasks): Average satisfaction score for the programme and topics covered in the programme in the exit survey		
	4 Intervention coherence (How did the participant feel in terms of understanding the tasks and performing them by himself): Participants’ report on what they learned during the programme		Evidence for perceived benefits and effectiveness of the intervention in the follow up interview.
	5 Opportunity costs (What were the benefits the participants perceived): Participants’ feedback		
	6 Perceived effectiveness (To what extent did the participant feel that strategy was effective): Participants’ report on what they learned during the programme		
	7.Self-efficacy (How confident and comfortable was the participant at performing the task): Average confidence score for each of the target behaviours in the safety training procedure document		

*Treatment is delivered by the research team. Hence no training sessions required

These criteria will be evaluated through an intervention checklist, direct observation, audio recording of the in-person intervention sessions and reported experience of the facilitators.

Additionally, the current study will recruit farmers who have opportunities to demonstrate the learnings from the intervention to a non-participant person. During the feasibility evaluation, the authors will examine the report from the recruiters to determine whether this criterion came up as a barrier to recruitment or retention. This is especially relevant as farming in Ireland is generally small scale, with an average farm size of fewer than 14 ha, and farmers regularly meet through discussion groups or similar events [50, 51]. Peer-to-peer demonstration and facilitated discussion present a unique opportunity for knowledge sharing and learning within the community.

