#### Acceptability of the intervention

A review of farm safety interventions observed that even when the researchers report the intervention and its delivery, they provide little to no information on perceived acceptability for the programme among participants [57]. Given that perceived acceptability reflects the extent to which the intervention was perceived as appropriate, the successful adoption of the intervention relies on it [58, 59].

During the intervention development phase, the study utilised the BCW framework to identify BCTs for inclusion in the intervention. As part of this process, the APEASE (Acceptability, Practicability, Effectiveness, Affordability, Spill-over effects, and Equity) criteria were utilised to ensure that the selected BCTs met the necessary criteria of being acceptable, practical and effective [23]. However, to evaluate the acceptability of the intervention and its components among participants, the study will use the Theoretical Framework of Acceptability (TFA) framework. The TFA framework is a comprehensive and flexible framework that provides a structured approach to understanding the acceptability of interventions. It enables researchers to explore how participants feel about the intervention and why they feel that way. The study will explore the seven component constructs of TFA: Affective attitude, Burden, Ethicality, Intervention coherence, Opportunity costs, Perceived effectiveness and Self-efficacy [59]. By breaking down the concept of acceptability into several domains, the TFA framework allows researchers to identify which aspects of the intervention are most important to participants and where there might be issues with acceptability. This information is essential for tailoring the intervention to meet the needs and preferences of the target population, which can increase its uptake and effectiveness.

The follow-up assessment involves an in-depth interview that will explore the participant’s retrospective perceptions of the acceptability of the intervention, the expectations and experiences of the intervention, and its key components.

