During the evaluation design phase, reported outcomes of previous farm interventions were considered while determining the factors for measuring the programme’s success. For example, farm safety literature suggests that 25–77% of the farmers contacted could be expected to agree to participate [63–67], and an average of 80–100% satisfaction was reported among the participants with the previous farm safety intervention programmes [9, 67, 68]. Since the study will be conducted in the summer, farmers’ busy work schedules and vacation plans are also expected to influence participation and retention [69]. To measure treatment fidelity, the study will adhere to the National Institutes of Health Behavior Change Consortium guidelines, which define high treatment fidelity as having more than 80% adherence to the intervention checklist [49]. The researchers will use the intervention checklist, which provides a clear outline of the key components of the intervention and serves as a guide for implementation. The researchers will evaluate adherence by comparing the actual implementation of the intervention to the checklist and assessing the percentage of key components that were successfully implemented. The criteria outlined in Table 1 are established a priori to evaluate the success of the study, specifically the feasibility of implementing the intervention, the extent to which participants received the intended intervention and the acceptability of the intervention among participants. If some of the criteria are not met, the authors will investigate the potential causes of failures and consider changes to the intervention components and its delivery methods before deciding whether to recommend the development of a future larger trial to test the effectiveness of the intervention.

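### Table 1 defines opportunity costs as benefits and gives coherence and perceived effectiveness one shared indicator, so the acceptability checklist has no measure of what farmers gave up

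*Protocol article*

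**What the plan says.** The section on acceptability of the intervention adopts the Theoretical Framework of Acceptability. It states that "The study will explore the seven component constructs of TFA". The reason given is that splitting acceptability into domains lets researchers "identify which aspects of the intervention are most important to participants and where there might be issues with acceptability", which the article treats as essential for tailoring the intervention.

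The acceptability checklist in Table 1 turns the constructs into seven items, each with a gloss and an indicator:

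- Item 1: "Affective attitude (How did the participant feel about the programme): Average satisfaction score for the programme in the exit survey".
- Item 2, burden: glossed as structure and ease of understanding; indicator, the satisfaction score for programme structure plus feedback.
- Item 3: "Ethicality (To what extent the strategy helped in performing the farm tasks"; indicator, the satisfaction score for the programme and the topics it covered.
- Item 4, intervention coherence: indicator, the participants' "report on what they learned during the programme".
- Item 5: "Opportunity costs (What were the benefits the participants perceived"; indicator, participants' feedback.
- Item 6, perceived effectiveness: the same indicator as item 4.
- Item 7, self-efficacy: the average confidence score for each target behaviour.

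The success criteria are 80% agreement on the exit survey, 80% of participants rating their confidence at 7 out of 10 or higher, and, for the follow-up interview, evidence of perceived benefits and effectiveness.

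**The concern.** A cost is what is given up and a benefit is what is gained. An item labelled as the first and defined as the second will be asked about, coded and reported in the wrong direction. It also duplicates ground that perceived effectiveness already covers.

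Sharing an indicator causes a different problem. A farmer may learn exactly how to mark a visibility zone and still doubt that it prevents accidents. If coherence and effectiveness are both read from what was learned, that farmer looks the same on both.

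Objective 3 is the acceptability of the active components. The data analysis section says that the Table 1 criteria were set in advance and that unmet criteria will be investigated before a larger trial is recommended. A programme that farmers find useful but too expensive in time could meet the interview criterion as it stands. The possibility is realistic in this setting: the event takes half a day, and the data analysis section says that farmers' "busy work schedules and vacation plans are also expected to influence participation and retention". That remark concerns recruitment and retention, so it shows that time pressure is plausible here. It does not by itself show a gap in the acceptability measures.

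**Working it through.** No formula applies and the plan gives no figure to reproduce. The check compares label, gloss and indicator for each item, using the acceptability checklist alone.

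| Item | Gloss agrees with plain meaning of label? | Indicator shared with another item? |
|---|---|---|
| 1 Affective attitude | Yes | In part, with item 3 (programme satisfaction) |
| 2 Burden | Limited to structure and ease of understanding | No; own structure score |
| 3 Ethicality | Glossed as helpfulness; the article gives no definition to test it against | In part, with item 1 (adds topics covered) |
| 4 Coherence | Yes | Identical to item 6 |
| 5 Opportunity costs | No; reversed | No; unspecified feedback |
| 6 Perceived effectiveness | Yes | Identical to item 4 |
| 7 Self-efficacy | Yes | No; own confidence score |

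Counts:

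- Gloss opposite to label: 1 of 7 (item 5).
- Identical indicator: 2 of 7 (items 4 and 6). Partly shared indicator: 2 of 7 (items 1 and 3). Together 2 + 2 = 4 of 7 are not cleanly separable on the listed indicator.
- Clearly distinct score of its own: 2 of 7 (items 2 and 7).
- Gloss or indicator that asks about time, money or work forgone: 0 of 7.

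Item 5 is unlikely to be a single misplaced word, because the interview criterion points the same way: it asks for benefits and effectiveness and names no cost.

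Next, could costs enter by another route in the article? Four places partly reach them:

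1. Objective 4 covers perceived barriers and enablers to taking part and completing.
2. The recruitment strategy records refusals and the reasons for them.
3. A feasibility row in Table 1 asks whether the programme, including the length of the event, is reasonable for participants.
4. The follow-up interview asks about barriers to the home tasks.

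None of these replaces item 5. Refusal reasons come from people who did not take part. A barrier is what obstructs someone, whereas a cost is also borne by those who finish. The Table 1 row that names barriers concerns setting up the event, as identified by facilitators.

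**The case against.** The strongest reply is that the interview is the main instrument. The data-collection entry beside item 1, apparently meant for all seven items, includes it, and the article says that it will explore the intervention's key components. The topic guide and the exit survey are additional files that are not shown, and either may already ask about costs or keep the constructs apart. With the four other routes to costs, a reader should not infer that the study is unable to show what taking part costs or which aspect of acceptability fails. The documents do not support that, and this part of the reply stands.

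Three other strong readings also fail. It is tempting to say that every construct merely restates satisfaction, or that self-efficacy alone has its own quantitative measure; the structure score for burden contradicts both. It is tempting to say that ethicality is wrongly defined because it should mean fit with farmers' values; the article lists the construct without defining it, so only the helpfulness gloss and the overlap with item 1 can be faulted from the text. And a favourable bias in the results is possible but not demonstrated: quantitative analysis is descriptive, and neither opportunity costs nor ethicality has a criterion of its own.

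What the reply does not remove is the table. Even if the guide asks about costs, the published framework would file the answers under a construct defined as benefits, and would read two constructs from one report of learning.

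**Conclusion.** The point holds in a limited form. Followed as written, the acceptability checklist inverts one construct of seven, gives two others the identical indicator, and lets a further two overlap in part. No acceptability indicator or success criterion captures what participants gave up. That conflicts with the article's own reason for using seven constructs.

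The conclusion rests on the plain meanings of cost and benefit and on the table's text, not on outside definitions. It concerns the listed indicators; how far the unseen topic guide and exit survey make up for them is unknown. The defect weakens the report on objective 3 but does not invalidate the study, and it should be corrected because the correction is cheap.

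**What to change.** Reword four items of the acceptability checklist:

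- Item 5: what participants had to give up (time, money, farm work) to attend the event and to carry out the three practices.
- Item 4: participants' understanding of the tasks.
- Item 6: whether participants think that the practices work.
- Item 3: an indicator distinct from item 1, with the gloss checked against, and matched to, the definition in the framework that the article cites.

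Where the topic guide lacks them, add one question for each item to the existing one-hour interview, at most four in all, and code each construct from its own question. For consistency, the interview criterion should also report costs alongside benefits and effectiveness.

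The price is a slightly longer interview; no extra participants, visits or instruments are needed. The article gives recruitment in August to September 2022 and is dated July 2023. If the interviews are already complete, the redefinitions can still govern the coding of the retained transcripts, and the report should state which constructs were not asked about directly.
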